### Primary outcome measurements

The primary outcome will be measured as between- and within-group differences in the Numerical Pain Rating Scale (NPRS) at the second and third assessments.

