**Methods/design:**

Patients with non-traumatic chronic neck pain (patient-centered care and active involvement of patients and the public) will be recruited via flyers displayed in hospitals and universities to participate in an RCT with two experimental and one control group designed to investigate the effects of PNE with online and face-to-face exercise interventions, and the control group received biomedical education + standardized physical therapy on neck pain and disability, psychological factors, and function in non-traumatic chronic neck pain. The outcomes will be measured at baseline, after PNE, and after 3 months of an exercise intervention. All outcomes are presented as mean ± SD, and statistical significance was set at *α* level of < 0.05. The normal distribution of the variables was verified by the Kolmogorov-Smirnov test, following a descriptive analysis.

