Online rehabilitation reduces the treatment cost and provides 24/7 online support for home exercises [30]. Supporting exercise at home is important because self-management consistency in exercise is a common problem in exercise therapy [31, 32]. Research shows the importance of continuity of exercise at home, because it has positive effects on pain and physical function [32] and cost reduction [30].

To our knowledge, no randomized control trial (RCT) has examined the differences in the effect of PNE with online and face-to-face exercise interventions in people with chronic neck pain. Therefore, the present study aims to investigate the differences between the effect of PNE with online and face-to-face exercise interventions on neck pain and disability, psychological factors, and function in non-traumatic chronic neck pain during COVID-19. We hypothesized that PNE with online exercise intervention could be more effective than PNE with face-to-face exercise intervention on neck pain and disability, psychological factors, and function in non-traumatic chronic neck pain during COVID-19.

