### Study participants and eligibility criteria

The patients with chronic non-traumatic neck pain who meet the following criteria will be accepted as participants in the trial: patients with chronic nonspecific and non-traumatic neck pain of at least 3 months, visual analog scale (VAS) greater than 3 from 10, both sexes range from 18 to 65, accept to take part in the research, and sign the information concept [27].

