### Outcome variables

All variables will be assessed initially (before intervention), after PNE (after 2 weeks), and after exercise intervention (after 3 months). The flow chart can be seen in Fig. 1. After filling in the questionnaires by the patients, they will be asked about taking any painkillers and psychological medication. The completed questionnaires will be handed over to a skilled psychiatrist who will be blind to assigning patients to study groups. The psychiatrist will consider if it is necessary for any of the patients to take any psychological medication.

Personal information about potential and enrolled participants will be collected, shared, and maintained to protect confidentiality before, during, and after the trial.

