### Statistical analysis

The study was designed to identify a 2-point difference in pain intensity (30%) assessed by the NPRS across groups, with an expected standard deviation of 2.5 points [55]. For the global perceived effect, there is a difference of 2 points on the scale, with 11 points ranging from − 5 to + 5 [39]. The other specifications were an alpha of 5% and a power of 80%, with a total of 288 patients. However, assuming a 20% drop in follow-up, we will enroll 360 individuals (88 patients per group). G*Power was used to calculate the sample size (GPower 3.0.10, University of Kiel, Germany). The intention-to-treat protocol was followed for post-treatment analysis. See the CONSORT diagram for details.

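### The primary outcome includes within-group pain change at two visits and names no primary contrast or time point, so uncontrolled improvement can count as a primary result

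*Protocol article*

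**What the plan says.** Under Primary outcome measurements, the protocol article reads: "The primary outcome will be measured as between- and within-group differences in the Numerical Pain Rating Scale (NPRS) at the second and third assessments". Under Outcome variables, those two assessments fall at 2 weeks, after the education, and at 3 months, after the exercise programme. The abstract describes "an RCT with two experimental and one control group".

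The level is given twice. The abstract says that "statistical significance was set at *α* level of < 0.05", and the Statistical analysis section uses "an alpha of 5% and a power of 80%, with a total of 288 patients". Neither place mentions an order of tests, a split of alpha or an adjustment.

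The Introduction is more specific about the question: "We hypothesized that PNE with online exercise intervention could be more effective than PNE with face-to-face exercise intervention on neck pain and disability". The sample size is set for a 2-point NPRS difference across groups with an SD of 2.5. Both of these are between-group statements. One entry criterion is "visual analog scale (VAS) greater than 3 from 10".

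**The concern.** Two separate problems sit in one sentence.

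The first is that within-group change is part of the primary outcome. A fall from baseline within an arm is a before-after comparison without a control. It mixes any treatment effect with natural course and with regression to the mean, which a minimum pain score at entry makes likely. All three arms, control included, receive education and exercises, so a fall in every arm is plausible even if the interventions are equivalent. A significant fall in one arm, or in one arm and not another, could then be reported as a primary finding.

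The second is that the between-group part names neither a contrast nor a visit. Three arms and two visits leave several results that could each be called primary at 5%, while the stated hypothesis is one contrast. The 2-week visit adds little to that hypothesis: Table 1 places the exercise phase, where the two experimental arms differ, after the 2-week education phase that they share.

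At stake is what the trial may conclude about its main question.

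**Working it through.** **Inputs from the protocol article.** Three arms; two post-baseline visits; alpha 5%; difference 2 points and SD 2.5 (Statistical analysis); 20% loss; 288 evaluable (Statistical analysis); 120 randomised (Allocation concealment mechanism and Discussion).

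**Assumptions not in the article.** Two-sided tests; a common improvement of 1 point (range 0.5 to 1.5); correlation between the two follow-up visits of 0.3 to 0.8; pre-post correlation r = 0.5. The last gives a change SD of 2.5 × √(2(1 − 0.5)) = 2.5.

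**The plan's own figure.** The article gives no familywise error rate to reproduce. Its 288 does not follow from its inputs: n per arm = 2 × (1.960 + 0.842)² × 2.5² / 2² = 24.5, so 25 per arm and 75 in three arms. The step 288 / 0.8 = 360 does reproduce, but 360 / 3 is 120 per arm, not the stated 88. These are separate matters, and the present point does not depend on them. Because the article gives conflicting sizes, two are carried through:
- 120 × 0.8 / 3 = 32 per arm
- 288 / 3 = 96 per arm

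**Number of comparisons, read literally.** Between groups: 3 pairs × 2 visits = 6. Within groups: 3 arms × 2 visits = 6.

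**Within-group tests at one visit, all arms improving equally.** One-sample t-test with noncentrality δ / (2.5 / √n). For δ = 1 the noncentrality is 2.26 at n = 32 (critical value 2.04) and 3.92 at n = 96 (critical value 1.99). With p the chance that one arm is significant, the chance for at least one of three is 1 − (1 − p)³.

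| Common fall | p, 32 per arm | at least one arm | p, 96 per arm | at least one arm |
|---|---|---|---|---|
| 0.5 | 19% | 48% | 49% | 87% |
| 1.0 | 59% | 93% | 97% | >99.9% |
| 1.5 | 91% | >99.9% | >99.9% | >99.9% |

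The true difference between arms is zero in every row.

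The chance that some arms but not all are significant is 1 − p³ − (1 − p)³. For a 1-point fall it is 72% at 32 per arm and 8% at 96 per arm.

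**Between-group tests under the null.** Simulation with 400,000 runs, allowing for shared arms and correlated visits.
- Six unadjusted pairwise tests: familywise error 22%, 21%, 20% and 18% at visit correlations 0.3, 0.5, 0.7 and 0.8.
- Three pairwise tests at one visit: 12%.
- One omnibus test at each of two visits: 9.6% at correlation 0.3, falling to 7.9% at 0.8. The value under independence is 1 − 0.95² = 9.75%.

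**Power for 2 points, 32 per arm (noncentral t).** At 5%: 88%. At 0.05/3: 77%. With baseline adjustment at correlation 0.5, the residual variance is multiplied by 1 − 0.5² = 0.75, which gives 95% and 89%.

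**The case against.** The best defence is that the article describes comparisons, not tests. It does not state twelve tests, pairwise t-tests, a model or a success rule. The wording also fits a single repeated-measures analysis with an overall group test. The 5% in the abstract is a general sentence, and the other 5% belongs to the sample size; neither excludes adjustment. Model, order of contrasts and multiplicity procedure are commonly left to an analysis plan, and that plan is not shown.

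Most of this stands against the multiplicity figures. A reader might infer that the trial has a primary false-positive rate near 20%. The article does not support that, because 18–22% needs unadjusted pairwise testing at both visits, which is nowhere stated. A reader might also infer that most such trials would show significance in some arms and not in others. That 72% holds only at 32 per arm with an assumed 1-point fall; it drops to 8% at the 96 per arm that the Statistical analysis section implies.

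The defence does not reach the within-group part. Within-group change and both visits are written into the primary outcome itself. An analysis plan could add an adjustment, but within-group change would still be primary until that sentence is changed. The chance of at least one significant arm rises with sample size, so a larger trial makes this worse.

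**Conclusion.** The point holds in a limited form. The primary outcome admits uncontrolled within-group change and leaves contrast and visit open, although the hypothesis and the sample size are both between-group.

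The within-group part is firm in principle. Its size, 59% to 97% per arm and 93% to over 99.9% for at least one arm, rests on an assumed 1-point common improvement and an assumed change SD of 2.5. A 0.5-point improvement brings the chance of at least one significant arm down to 48–87%.

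The between-group part is conditional: about 18–22% under unadjusted pairwise tests at both visits, about 8–10% under an omnibus test at each, and possibly controlled in a plan not shown. No success rule is written, so the text permits a claim based on within-group change; it does not show that one is planned.

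**What to change.** - Define the primary outcome as the between-group difference in NPRS at the third assessment, adjusted for baseline NPRS.
- Name online versus face-to-face as the primary contrast, in line with the stated hypothesis.
- Handle the two contrasts of education-plus-exercise against control with a prespecified multiplicity procedure, for example Holm across all three contrasts. A fixed sequence starting with online versus face-to-face is an alternative that keeps the full 5% for the first test. Its price is that neither control comparison can be formally tested if that first test fails.
- Make the 2-week differences secondary, and report within-group changes descriptively without p-values.

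**Cost.** No new data are needed, since baseline NPRS is already collected. Fewer results can be called primary. At 32 per arm, testing a contrast at the Bonferroni level (the strictest Holm step) lowers power for 2 points from 88% to about 77% without baseline adjustment, or from about 95% to 89% with it, at an assumed baseline correlation of 0.5. At 96 per arm, power stays above 99%. Completion was planned for May 2022 and the article appeared in December 2022, so this is more than a wording change: it needs a dated amendment or a prespecified analysis plan fixed before unblinding.

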#### Numerical Pain Rating Scale (NPRS)

The scale is 11 points for pain reporting. This is the most common pain reporting scale. The patient will choose a number according to the rule (0–10) that best indicates the severity of his pain. The number zero indicates no pain and 10 indicates the most severe or worst pain. (There are different types of numbers from 0 to 10 that one can choose). The scales are categorized as follows: painless (0), mild pain (1–3), moderate pain (4–6), and severe pain (7–10), but these categories do not necessarily reflect the patient’s meanings and for any assessments are poor. These categories may be used to set goals for the outcome of the intervention. NPRS can be done orally (by phone) or graphically. The validity of the NPRS has been shown in patients with rheumatism and other chronic pain conditions (pain > 6 months), ICC has been reported to be 0.95–0.86.40. The MDC reported from the 11-point NPRS is 0.45 [39].

### Secondary outcome measurements

#### Neck Disability Index (NDI)

The Neck Disability Index (NDI) is a questionnaire [40] consisting of ten sections that show the effect of neck pain on a person’s daily activities. The ten sections include determining the severity of pain, activities such as personal care, studying, headaches, concentration, work, driving, sleep, lifting, recreation, and entertainment.

In each part, the patient receives a score between 0 and 5, with 0 indicating no problem and a score of 5 indicating the most problem. The total score obtained from the neck pain and disability questionnaire is between 0 and 50, which is in five levels: 0–4 without disability, 5–14 low disability, 15–24 moderate disability, 25–34 severe disability, and 35–50 disability. Its reliability and internal coherence are well reported [40, 41]. In cases where the activities mentioned in the questionnaire are not in the person’s daily schedule, the scores are adjusted and calculated based on the percentage of the total score. In this trial, the disability index, a score between 15 and 30 or 30 to 60% of the total adjusted score, was considered [40]. It has been shown that this questionnaire has high validity (correlation with Magill pain questionnaire = 0.70) and excellent reliability (ICC = 0.89) [42]. Its reliability and internal consistency are well reported (ICC = 0.80) (109) [43]. The least clinically significant difference (MCD) in people with chronic nonspecific neck pain is 20% [44].

#### Pain Catastrophic Scale (PCS)

The Pain Catastrophic Scale (PCS) is used to assess catastrophic pain perceptions. PCS consists of 13 items scored on a 5-point scale. The total score is between 0 and 52. The higher scores indicate a more severe pain disaster [45]. The ICC has been reported to be 0.87–0.87 for PCS [46].

#### Depression, Anxiety, and Stress Scale-21 (DASS-21)

DASS-21 applies psychological distress components (depression, anxiety, stress) on a 21-item ranking scale with scales for each item 0 “does not apply to me at all” to 3 “very” or most of the time [47, 48]. This questionnaire has good structural validity and provides improved normative data and rating scales to help describe the clinical severity (mild/moderate/severe/very severe) for each scale. Scores greater than 20 (depression), more than 14 (anxiety), and more than 25 (stress) indicate a “severe” rating [47, 48]. Reliability for depression anxiety and stress is 0.96, 0.89, and stress 0.95, respectively [49, 50].

#### Deep Neck Flexor Endurance Test

Neck flexor muscle endurance will be measured using Grimmer’s deep neck flexor endurance test [51]. The person was placed in the supine position on the examination bed with his hands on the bed next to his body and puts the soles of his feet on the bed. He was asked to bend his chin towards his neck, keep his head about 2.5 cm away from the bed, and then maintain this position as much as possible [51]. The length of time the patient was able to maintain this position will be recorded. The test shows the activation and isometric endurance of the deep cervical flexors as well as their interaction with the superficial cervical flexors. If the position is not fully maintained, the test will be stopped. The validity of this test has been confirmed [52]. No MDC seems to have been reported for this test.

### Adherence

It is believed if patients’ autonomy, perceived competence, and relatedness are satisfied, patients’ participation in treatment will be more autonomous and less controlled. This will occur when the patient will be given valued benefits of the treatment by his/her therapist or healthcare and then willing to participate. Also, the patient’s participation in the treatment could be enhanced through a satisfying relationship with his/her therapist [53]. Through this process, the researchers will try their best for patients to feel that the treatment is potentially the best thing for their health and is consistent with their goals [54].

### Statistical analysis

The study was designed to identify a 2-point difference in pain intensity (30%) assessed by the NPRS across groups, with an expected standard deviation of 2.5 points [55]. For the global perceived effect, there is a difference of 2 points on the scale, with 11 points ranging from − 5 to + 5 [39]. The other specifications were an alpha of 5% and a power of 80%, with a total of 288 patients. However, assuming a 20% drop in follow-up, we will enroll 360 individuals (88 patients per group). G*Power was used to calculate the sample size (GPower 3.0.10, University of Kiel, Germany). The intention-to-treat protocol was followed for post-treatment analysis. See the CONSORT diagram for details.

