### Allocation concealment mechanism

After the initial evaluation, patients will be randomly assigned to one of three study groups (PNE as an experimental group) and pain biomechanics education (control group) by selecting numbers from 1 to 120, which will be pre-prepared and packaged in sealed envelopes by an independent person. The randomization sequence will not be disclosed until patients complete their baseline assessments. The statistician and the assessor will be blind to the group allocation. Patients will not be blind to the intervention, but do not know which group will be treatment therapy. The three groups in the study will be monitored by a physiotherapist and a corrective movement instructor.

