## Discussion

For several years, treating patients with chronic pain has been more evaluated and has been given more attention due to the burden of prevalence and cost that the patient, his/her family, and society have to handle [56]. This RCT aims to investigate the differences between the effects of PNE with online and face-to-face exercise interventions on neck pain and disability, psychological factors, and function in 120 patients with non-traumatic chronic neck pain during the lockdown imposed by COVID-19. The outcomes of this RCT may help patients with neck pain living in lockdown to overcome their pain through webs which is more cost-effective and time-consuming than face-to-face treatment.

Tele-rehabilitation is home-based, professionally guided training sessions accessed via telecommunication devices such as video calls or pre-recorded classes. It is mostly used nowadays because of COVID-19, which allows treatment of patients without the risk of infection for neither the patient nor the health professionals [57].

Technological adjunctive techniques, such as remote health, have been used successfully in the rehabilitation of conditions such as stroke [58] and orthopedic surgery [59] and promise to provide psychological treatment. Such approaches have not yet been used in chronic neck pain exercises; however, evidence suggests that inactive treatment is not necessary for neck pain conditions. Instead, active treatment approaches that improve patients’ self-efficacy are preferred because of the strong evidence that they can be presented in more innovatively ways than traditional face-to-face sessions.

Also, the results of a clinical trial by Traeger et al. (2018) have shown that the PNE approach can reduce possible referrals for health care over 3 months (but not 12 months) compared to the control group [60]. Given the heavy financial burden of chronic musculoskeletal pain on health care, PNE has been shown to reduce intra-group health care consumption in a sample of musculoskeletal pain and can therefore be considered a cost-effective intervention [61, 62].

In summary, the protocol of this RCT is inexpensive and needs minimal equipment. However, to be sure about the persistence of the results, it is suggested that this approach could be further investigated in a follow-up of 12 months.

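### The sample-size paragraph contradicts itself (360 enrolled against 88 per group, which is 264), conflicts with the 120 given elsewhere, and its 288 does not follow from its own inputs

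*Protocol article*

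**What the plan says.** The Statistical analysis section of the protocol article gives the design inputs. The aim is put this way: "The study was designed to identify a 2-point difference in pain intensity (30%) assessed by the NPRS across groups". The SD is taken to be 2.5 points, and the remaining inputs are "an alpha of 5% and a power of 80%, with a total of 288 patients". The section then allows for loss to follow-up and sets the enrolment: "assuming a 20% drop in follow-up, we will enroll 360 individuals (88 patients per group"). It names G*Power as the software but not the test, the sidedness or any adjustment for several comparisons.

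The article describes three groups throughout (Sequence generation, Allocation concealment mechanism, and the list of treatment programmes under Fig. 1).

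Two other sections give a different size. Under Allocation concealment mechanism, patients are assigned to the three groups "by selecting numbers from 1 to 120, which will be pre-prepared and packaged in sealed envelopes by an independent person". The Discussion describes the trial as one conducted "in 120 patients with non-traumatic chronic neck pain during the lockdown imposed by COVID-19".

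**The concern.** One sentence gives two enrolment targets that cannot both be true in a three-group trial, and two other sections give a third. The number to randomise is a core design figure, and here the concealment mechanism is tied to one of the three values. If 360 was meant, a series that ends at 120 covers one third of the patients, and the article does not say how the others would be allocated. If 120 was meant, the published justification belongs to a different trial. In either case a reader of the results could not tell whether the final number was completion, a shortfall or over-recruitment.

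The 288 from which the paragraph starts also looks too large for the inputs beside it, so the conflict may begin before the dropout step.

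**Working it through.** **Inputs.** From Statistical analysis: difference 2 points, SD 2.5, so d = 2/2.5 = 0.8; alpha 5%; power 80%; 288 patients before loss; loss 20%; 360 enrolled; 88 per group. From Allocation concealment mechanism and Discussion: 120. Assumptions not stated in the article: two-sided tests and equal groups (implied by a single per-group number).

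**1. The plan's dropout step.** 288/(1 − 0.20) = 360. This reproduces, so 288 and 360 belong together.

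**2. The per-group figure.**
- 360/3 = 120 and 288/3 = 96. Neither is 88.
- 3 × 88 = 264, which is 96 patients (27%) below 360.
- 264 × 0.8 = 211.2, which is not the 288 stated just before.

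**3. The allocation series.** 120/360 = 33% and 120/264 = 45%. A series of 120 covers neither total.

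**4. Does 288 follow from the inputs?**
- Pairwise comparison, normal approximation: n = 2(1.960 + 0.842)² × 2.5²/2² = 24.5, so 25 per group. The t test gives 26 per group, or 78 in total.
- Pairwise t test with Bonferroni over three pairs (alpha 0.05/3): 35 per group, or 105 in total.
- Pairwise, one-sided, normal approximation: 20 per group, or 60 in total.
- Pairwise at 90% power, normal approximation: 33 per group (99 in total), or 43 (129 in total) with Bonferroni.
- Three-group ANOVA, one mean differing by 2: f = 0.377, 72 in total with equal groups.
- Three-group ANOVA, means 0, 1, 2: f = 0.327, 94 in total, or 96 with equal groups.

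None of these gives 288.

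**5. A possible origin, by inference only.** The last ANOVA result gives 96 in total, and 96/0.8 = 120, the figure in the other two sections. Also 3 × 96 = 288. A total of 96 may have been read as a per-group number and multiplied by three. The article does not say so, and this would not explain 88.

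**6. What each target would deliver** (two-sample t test, SD 2.5, two-sided 5%, 20% loss):

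| Enrolled | Evaluable per group | Pairwise power for 2 points | Same, Bonferroni over 3 pairs | Difference detectable with 80% power, unadjusted |
|---|---|---|---|---|
| 120 | 32 | 88% | 77% | 1.78 |
| 264 | 70 | 99.7% | 98.9% | 1.19 |
| 360 | 96 | over 99.9% | 99.9% | 1.02 |

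The normal approximation gives 89% and 79% in the first row.

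**The case against.** **The trial can be run as described.** The allocation text works at 120: one sealed, numbered series for three groups, and the Discussion independently gives the same size. This stands. It would be too strong to say that the trial cannot be executed. What fails is the match between the sample-size paragraph and the other two sections.

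**The 120 might be per group.** Since 360/3 = 120, the envelopes could be reconciled with 360 on that reading. But the allocation section describes one series serving all three groups, the Discussion gives 120 as the patients of the trial, and 88 per group would still be wrong. The CONSORT diagram, to which the paragraph refers for details, is not shown in the text at hand and might settle which figure was intended. It cannot make 3 × 88 equal 360.

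**A reader might infer that the trial is underpowered**, because 264 enrolled leaves 211 and the plan asks for 288. The figures do not support this. The 288 is itself not derivable, and the smallest target still detects 1.78 points, less than the planned 2, in an unadjusted pairwise comparison. Only with Bonferroni over three pairs does 120 fall slightly short of 80%, and the article does not state such an adjustment.

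**A reader might also infer** that patients were allocated outside the concealed list, or that the sponsor could stop wherever convenient. The article states neither and describes no interim look. The first is a question to ask if 360 was the target; the second is only a risk left open by having several targets on file.

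**Conclusion.** The concern holds as a contradiction about the trial's intended size and its allocation list. The sample-size sentence gives both 360 and 264, two other sections give 120, and nothing in the text reconciles them. In addition, 288 does not follow from the stated difference, SD, alpha and power: the variants tried at the stated 80% power need 60 to 105 evaluable patients in total.

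The contradiction in the totals is plain arithmetic and rests only on there being three equal groups. The statement about 288 assumes a comparison of group means with SD 2.5. The global perceived effect, also mentioned in the paragraph, has no SD and is not among the listed outcomes, so it cannot supply the missing derivation. Lack of power is not demonstrated at any of the three sizes. The point must be fixed because the number randomised and the concealed list have to refer to the same trial.

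**What to change.** State the single total and per-group target that was in force at randomisation. Show the calculation that gives it, including the test, the sidedness and any multiplicity adjustment. Then align Statistical analysis, Allocation concealment mechanism and Discussion.

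- **If the target was 120:** write 40 per group and 32 evaluable per group after 20% loss. Replace 288, 360 and 88. State the power as about 88% per unadjusted pairwise comparison, or about 77% with Bonferroni over three pairs.
- **If the target was 360:** correct 88 to 120 per group, justify 288, and report how patients beyond number 120 were allocated with concealment.
- **If 264 was meant:** correct 360 and 288, justify 88 per group, and report the allocation beyond number 120 in the same way.

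The choice should follow the record and not convenience. The Trial status section says that the trial is underway, with completion planned for May 2022, and the article was published in December 2022. Picking the smallest figure now, or extending the list as if it were still unused, would be a decision after the fact.

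The cost is a check of the allocation records, a dated correction and rewording in three sections. Documenting the true target requires no extra patients.
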